### Data collection and outcomes

#### #Aim I: effectiveness

Two trained researchers, blind to the patients’ group, will be responsible for the organization and data collection process. Every 30 days after the date of randomization, and over a 1-year period, the participants of both groups will receive a text message (SMS API (twilio.com)) with a yes/no question regarding LBP recurrence (In the last month did you have pain in your back, with an intensity equal or greater than 2, on a scale where “0” means no pain and “10” the worst pain imaginable and lasting at least 24 h?). This question is based on the definition of LBP recurrences: “the return of LBP with a minimum duration of 24 hours, with a pain intensity ≥ 2 on an 11-point numerical scale, preceded by a minimum period of 30 days without pain” [53]. All text messages will be sent and received through a specific SMS platform. In the presence of a LBP recurrence, the researchers will contact the participant by telephone to answer to a brief survey concerning the date of the recurrence and its impact (if the episode was severe enough to limit activity and/ or to cause care seeking), and to fulfil the self-reporting instruments (Table 1).

In the absence of a LBP recurrence, the researchers will contact the participants at three fixed data points: 3, 6 and 12 months after baseline, to fulfil the NPRS, Roland-Morris Disability Questionnaire (RMDQ), Musculoskeletal Health Questionnaire (MSK-HQ) and EuroQol (EQ-5D-3 L) (Table 1). The estimated patient’s burden to answer all the questionnaires is approximately 15 min. In addition, the participants’ medical records will be reviewed every 3 months. Data on any additional medical consultations, medication or imaging tests prescribed, referral to other interventions or to other medical specialities or services or sickness certificates will be recorded on the patient’s CRF.

Participants will remain on the trial unless they choose to withdraw consent, or they fail to answer three consecutive follow-up text messages. To prevent withdrawals and when a participant does not answer to 3 SMS text message or is not available at fixed follow-up time points, a maximum of three additional attempts will be made by telephone call.

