The primary outcome of the study will be the risk of LBP recurrence, i.e. the percentage of participants experiencing one or more episodes of LBP recurrence within a 12-month follow-up period. Secondary outcomes include pain intensity, functional disability, musculoskeletal health and HRQoL. Pain intensity will be measured by a NPRS (11-point version). The NPRS has proven to be valid and reliable in patients with LBP [54, 55]. Disability status and HRQoL will be evaluated through the Portuguese versions of the Roland Morris Disability Questionnaire (RMDQ) and the EQ-5D, 5 L. Both self-reported measurement instruments have been cross-culturally validated to Portuguese language and showed good to excellent psychometric properties [56, 57]. The Portuguese version of the Arthritis Research UK Musculoskeletal Health Questionnaire (MSK-HQ) will be used to measured musculoskeletal health and 12 related subdomains (pain severity, physical function, work interference, social interference, sleep, fatigue, emotional health, physical activity, independence, understanding, confidence to self-manage and overall impact). The original and Portuguese version of MSK-HQ showed adequate psychometric properties in people with musculoskeletal pain [58–60].

Costs data will be collected to both groups from medical health records, and they will consist of all back pain-related recourse used within primary health care by each participant. For the MyBack group, the costs related to the MyBack programme (costs per session; costs of training physiotherapists; costs of materials and transport) will also be collected.

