### Sample size (Aim I: effectiveness)

The sample size was estimated to the primary outcome (risk of recurrence) and based on recurrence rates described in previous studies. Assuming a recurrence proportion of 40% in 12 months [11], an alpha value of 0.05 and a power of 80%, a sample size of 81 participants per group will be necessary to detect a difference of, at least, 20% between the two groups (relative risk = 0.50) [14, 63]. The choice of the minimal clinically relevant difference was informed by a previous systematic review [14] and was considered realistic considering the study hypothesis. Based on previous studies carried out in the same settings [64], it is expected a dropout rate of 5% during the MyBack programme and a 10% loss of participants during follow-up. Therefore, the total sample size to be recruited will be 186 participants, 93 for each group.

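### No stated contact recovers recurrence status for one or two missed monthly texts, because text-triggered calls start only at three, so the any-recurrence primary outcome can stay undetermined

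*Protocol article*

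**What the plan says.** All references are to the protocol article.

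- **Collection (Data collection and outcomes, Aim I).** "Every 30 days after the date of randomization, and over a 1-year period, the participants of both groups will receive a text message". The question covers one month: "In the last month did you have pain in your back, with an intensity equal or greater than 2".
- **Exit rule (same section).** Participants stay in the trial unless they withdraw consent or "they fail to answer three consecutive follow-up text messages".
- **Telephone rule (same section).** To prevent withdrawals, "a maximum of three additional attempts will be made by telephone call" "when a participant does not answer to 3 SMS text message or is not available at fixed follow-up time points". There are thus two triggers: three unanswered texts, or unavailability at a fixed time point.
- **Fixed contacts (same section).** Participants without a recurrence are contacted at "3, 6 and 12 months after baseline, to fulfil the NPRS, Roland-Morris Disability Questionnaire (RMDQ"), the MSK-HQ and the EuroQol. Table 1 agrees: the row for LBP recurrences is marked in the monthly column and not in the 3-, 6- and 12-month column.
- **Record review (same section).** Medical records are reviewed every 3 months for consultations, prescriptions, referrals and sickness certificates.
- **Primary outcome (same section).** "the percentage of participants experiencing one or more episodes of LBP recurrence within a 12-month follow-up period".
- **Planned loss (Sample size).** 5% dropout during the programme and "a 10% loss of participants during follow-up".
- **Missing data (Data handling and analysis plan).** Multiple imputation.

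**The concern.** The outcome is asymmetric. One yes settles it, but a no requires all 12 windows to be answered. Because each text looks back one month, the next text does not cover a skipped month. As written, a participant who misses one or two texts triggers no call on that account, and the contacts that do take place are not listed as asking about the skipped window.

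If the three texts in the telephone rule are meant to be consecutive, the calls begin at the moment the exit rule is met, about 90 days after the last answered text. That is late for a step intended to prevent withdrawal.

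Two things are at stake. If gaps are read as no recurrence, events are lost, and the relative risk is distorted if response differs by arm. If gaps are imputed, the model supplies primary outcomes that a short call could have obtained.

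**Working it through.** **1. The plan's own figure.** Inputs from the Sample size section: 40% vs 20%, alpha 0.05 (taken as two-sided), power 80%. With the pooled two-proportion formula, n = [1.96·√(2·0.3·0.7) + 0.8416·√(0.24 + 0.16)]² / 0.20² = (1.270 + 0.532)² / 0.04 ≈ 81.2. The plan states 81; rounding up gives 82. Power at 81 is 79.9%. The recruitment target follows from 81 × 1.15 = 93.15, so 93 per group and 186 in total. The sample size reproduces and is not in dispute here.

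**2. Assumptions not in the documents.** Each text goes unanswered with probability m, independently. Recurrence has a constant monthly hazard h that gives 40% and 20% at 12 months: h = 1 − 0.6^(1/12) = 0.0417 (control) and h = 1 − 0.8^(1/12) = 0.0184 (MyBack). The exit rule is not applied.

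**3. How often gaps arise.** At least one missed text: 1 − (1 − m)^12. Three in a row at some point: recursion over the 12 texts.

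| m | any missed text | three in a row |
|---|---|---|
| 2% | 21–22% | 0.01% |
| 5% | 46% | 0.1% |
| 10% | 72% | 0.9% |
| 20% | 93% | 6.5% |

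Under independence, nearly all participants with gaps never reach three consecutive misses. Clustered non-response would lower the second column and raise the third. If the telephone rule counts any three misses, consecutive or not, more participants reach it: 11% at m = 10%.

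**4. Undetermined outcomes.** No observed yes and at least one unanswered window: (1 − h(1 − m))^12 − ((1 − m)(1 − h))^12. At m = 10%, control: 0.632 − 0.169 = 0.463; MyBack: 0.818 − 0.226 = 0.592.

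| m | control | MyBack |
|---|---|---|
| 2% | 14% | 18% |
| 5% | 29% | 38% |
| 10% | 46% | 59% |

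**5. How many of these hide a recurrence.** If gaps count as no, the observed risk is 1 − (1 − h(1 − m))^12. At m = 10% this is 36.8% and 18.2%. The recurrences lost are therefore 40 − 36.8 = 3.2 points (control) and 20 − 18.2 = 1.8 points (MyBack). Of the undetermined participants, 3.2/46.3 ≈ 7% and 1.8/59.2 ≈ 3% had a recurrence; the rest are true non-events.

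**6. Effect on the comparison at m = 10%.** Relative risk 18.2/36.8 = 0.49. Power is 76% at 81 per group, 79.5% at 88 (93 less 5%) and 82% at 93. The larger numbers apply because participants whose gaps are counted as no remain in the denominator.

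**7. Differential response.** With an assumed 15% non-response in controls and 5% in MyBack, the observed risks are 35.1% and 19.1%, and the relative risk is 0.54 instead of 0.50. With the split reversed they are 38.4% and 17.3%, and it is 0.45.

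**The case against.** Several points on the other side stand.

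- **Participants with gaps are not abandoned.** A reader might infer that calls start only after three missed texts and that one or two missed months are never followed up. The documents do not support that. Unavailability at a fixed time point is a second trigger, participants without a recurrence are contacted at 3, 6 and 12 months whatever texts they missed, and records are reviewed quarterly. What remains is narrower: none of these is stated to ask about recurrence in a missed month. Record review cannot replace the question, since the Background section puts care seeking at 40% of people with a recurrence.
- **The calls need not come after exit.** The exit rule says consecutive and the telephone rule does not, and the stated purpose is to prevent withdrawal. It cannot be said that chasing starts only once participation has ended, only that the two rules coincide on one reading.
- **The size is assumed.** The protocol gives no text non-response rate, so it does not show that many participants are affected. The undetermined shares are also not comparable one for one with the planned 10% loss, which counts lost participants rather than missing windows, and imputation can draw on the answered months.
- **An article condenses.** Call scripts may be in the full protocol or the announced data management plan. However, this article states its own trigger and the content of its own contacts, and Table 1 agrees with the text. An analysis plan cannot recover answers that were never requested.

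**Conclusion.** The point holds as a weakness in how the primary outcome is collected. As written, the text-based trigger is three unanswered texts, each text covers one month, and no stated contact closes a shorter gap. For anyone without a yes, a single missed month leaves the outcome undetermined.

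The consequence is probably modest. Under independent non-response of 2% to 10% per text and a constant hazard, both assumed, 14–46% of controls and 18–59% of MyBack participants would be undetermined, mostly true non-events. Reading gaps as no costs about 4 points of power at 10% with 81 per group, and little or none relative to the 80% target with 88 to 93. Bias in the relative risk needs non-response that differs by arm. This is plausible, because MyBack participants have 12 supervised sessions and controls one short appointment, but the documents do not show it. The results do not support a claim that the trial is underpowered or its primary comparison invalid. They support a cheap improvement.

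**What to change.** 1. At each 3-, 6- and 12-month contact already scheduled, also ask the recurrence question, with the date, for every 30-day window still unanswered. Mark this in Table 1. The date also serves the planned log-rank comparison of time to first recurrence.
2. Make the telephone attempts after the first unanswered text, so that they come before the three-text exit rule can apply.
3. Reconcile the two rules: state whether the three texts in the telephone rule are consecutive, and that exit is declared only after the attempts have failed.

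**Cost.** Step 1 adds almost nothing to existing contacts. Step 2 means following up about 186 × 12 × m texts: roughly 45, 112 or 223 over the follow-up year at m = 2%, 5% or 10%, each with up to three attempts by the same two researchers. For the primary outcome this is an upper limit, since a participant with a recorded recurrence needs no further chasing. Step 3 is wording. The drawback is recall: under step 1 alone, a window missed just after month 6 would be asked about five to six months later. Step 2 largely avoids this.

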#### #Aim II: implementation

A mixed methods approach will be implemented in parallel with the effectiveness study and will help to understand the study processes or underlying mechanisms in relation to context, setting, professionals and patients. The exploration of feasibility, acceptability, fidelity, and contextual determinants of change is expected to provide knowledge that will improve the success of the implementation of different study tasks, such as the delivery of a training programme for physiotherapists or the provision of care. This stage will be informed by the Behaviour Change Wheel guidance [37]. Additionally, this knowledge will provide an opportunity for future triangulation of data obtained from other study stages and data. For this purpose, information about the perceptions and experiences of all stakeholders, namely patients, health professionals and HUs coordinators, and participation data will be collected. This phase will be informed by the Medical Research Council (MRC) guidance for the development and evaluation of complex interventions and the conceptual model of implementation research proposed by Proctor et al. (2011) [61] as well as the RE-AIM Planning and Evaluation framework [62] to evaluate implementation outcomes and its potential to scale-out across primary care.

Focus groups with patients, health professionals and HUs coordinators, will be carried throughout the implementation of MyBack study. Focus groups with HUs coordinators and health professionals will be focused on the exploration of their perceptions regarding the feasibility, acceptability, and fidelity of delivery of the intervention, considering the competences needed as well as the resources available. Information about additional facilitators and barriers will be collected in order to identify contextual determinants of change that were not identified prior to implementation and should be addressed by the research team. Focus groups with patients will be held as they acknowledge them as active participants in health interventions. These focus groups will explore the fidelity of receipt, that is, fidelity with which the content of the intervention is received by patients, as well as the acceptability of the intervention, barriers, and facilitators for the maintenance of exercise in the long term.

A total of 5 focus groups, including a minimum of 6 and maximum of 8 participants per group, will be carried out throughout the implementation of the MyBack study: 1 with HUs coordinators from the 3 PCC; 2 with health professionals from the 3 PCCs; 2 with patients. Thus, a minimum of 30 participants (6 HUs coordinators; 12 health professionals; 12 patients) are expected to be purposively selected from those who are going to participate in the study, by receiving or delivering MyBack programme or coordinating services for its implementation. To be included, patients are expected to have attended to a minimum of 12 treatment sessions. The focus groups will have an expected duration of 90 min per group and will be carried out by videoconference. All focus groups will be held by 2 researchers ([name]) with previous experience in facilitating focus group discussions. The discussions will be based on a semi-structured interview schedule previously developed and tested in pilot interviews. All focus groups will be audio-recorded and transcribed verbatim.

Additionally, study enrolment and participation data will be considered to evaluate the reach of the project in each practice by tracking the proportion of eligible patients referred to the study. Patients` adherence, defined as the completion of 12 or more treatment sessions, will be measured for all participants randomized into the MyBack group.

### Sample size (Aim I: effectiveness)

The sample size was estimated to the primary outcome (risk of recurrence) and based on recurrence rates described in previous studies. Assuming a recurrence proportion of 40% in 12 months [11], an alpha value of 0.05 and a power of 80%, a sample size of 81 participants per group will be necessary to detect a difference of, at least, 20% between the two groups (relative risk = 0.50) [14, 63]. The choice of the minimal clinically relevant difference was informed by a previous systematic review [14] and was considered realistic considering the study hypothesis. Based on previous studies carried out in the same settings [64], it is expected a dropout rate of 5% during the MyBack programme and a 10% loss of participants during follow-up. Therefore, the total sample size to be recruited will be 186 participants, 93 for each group.

### Data handling and analysis plan

A data management plan will be developed in advance entailing data collection procedures, missing data management, coding, and entry of variables in the electronic database. An independent researcher blind to the intervention groups will be responsible for transferring the patients’ data to the electronic database. All data will be stored in a coded format and, thus, unreadable without the codebook previously developed and kept securely under principal researcher responsibility. A data audit will be conducted every 3 months. Discrepancies between original data and database, and missing data, will be checked and corrected. Any missing values will be accounted for using multiple imputation methods.

#### #Aim I: effectiveness

To assess the effectiveness of the MyBack programme, a quantitative analysis of primary and secondary outcomes will be made using multivariable regression models. All quantitative analysis will be conducted by a statistician who will be masked to the intervention groups. The analyses will follow the intention-to-treat principle. Between-group differences for the primary outcome (risk of LBP recurrence) will be analysed using relative risk reduction (95%IC and significance level of *p* ≤ 0.05). Secondarily, survival curves for each group will be described and compared (log-rank test) using the days from randomization to the first episode of recurrence. Scores of pain intensity, disability, musculoskeletal health and HRQoL will be assessed for outliers, normality and homogeneity. In the case of parametric distribution, the differences between the two groups over time will be analysed using two-way repeated measures ANOVA. If significant, the Bonferroni post-hoc test will be used. In addition, a subgroup analysis will be performed according to potential differences between the participants who adhered or did not adhere to the experimental intervention.

The cost-effectiveness analysis will be developed from the perspective of the health care provider. All costs will be calculated for each participant and indexed in Euros for the reference year 2023. Quality-adjusted life years (QALYs) will be calculated with the EQ-5D, 5 L. Between-group differences for costs, QALYs and years of life gained will be analysed following the non-parametric bootstrap method. A cost-effectiveness analysis will be conducted using the incremental cost per QALY ratio.

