### Baseline assessment

After eligibility criteria have been confirmed, participants will attend a baseline assessment. All participants will complete the baseline assessment on-site that will include a questionnaire of prognostic factors for LBP recurrence and long-term disability [33–35] and specific instruments to assess pain intensity, functional disability, musculoskeletal health, and health-related quality of life (HRQoL). A description of the study measures is presented in Table 1.

**Table 1 Tab1:** Overview of study measurement

Construct/ Variables	Instrument/ Test	Time point			
		Baseline	Monthly	3, 6 & 12-months	
Demographics	Self-reported questionnaire [33–35]	x			
Clinical		x			
Work Situation**		x	x		
LBP recurrences	The return of LBP with a minimum duration of 24 h, with a pain intensity ≥ 2 on an 11-point numerical scale, preceded by a minimum period of 30 days without pain [32]		x		
Pain intensity**	Numeric Pain Rating Scale (0 to 10) [54, 65]	x	x	x	
Functional Disability**	Roland Morris Disability Scale (0 to 24) [56]	x	x	x	
Musculoskeletal Health (Subdomains: pain severity, physical function, work interference, social interference, sleep, fatigue, emotional health, physical activity, independence, understanding, confidence to self-manage and overall impact)	Musculoskeletal Health Questionnaire (0 to 56) [60, 66]	x		x	
Health-related Quality of Life	EuroQol, 5 dimensions, 5 levels (EQ-5D-5 L) questionnaire (0 to 1) [57]	x		x	
Aerobic capacity*	6-minute walking test [40]	x			
Trunk and lower limb resistance*	Trunk flexor test; Side bridge; Biering-Sörensen test; 60s sit to stand test [41–45]	x			
Trunk and lower limb flexibility*	Sit-and-reach test; Flexion and extension Schober test; Modified Thomas test [46–48]	x			
Motor Control*	Aberrant movement pattern and prone instability test [49, 50]	x			
Health care utilization and LBP Treatments (medical consultations, medication or imaging tests prescribed, referral to other interventions or to other medical specialties or services or sickness certificates) **	Self-reported questionnaire	x	x	x	

*MyBack group only; **Also measured when participants report a LBP recurrence in the screening that occurs every month.

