### Randomization and blinding

A randomization scheme will be developed prior to the beginning of the trial, for each HU, by an independent statistician. The randomization will be performed using block randomization (randomly permuted block sizes 4 and 6) in a 1:1 ratio and stratified by HU. According to the randomization scheme, opaque envelopes, sealed and numbered consecutively, indicating the intervention that the participant will receive, will be prepared, and provided to the different local physiotherapists. Immediately after baseline assessment, the PT will open the sequence opaque envelope previously received from a centralized randomization service to allocate the patient to the MyBack (exercise, behaviour change and usual care) group or usual care group. Due to the nature of the study and interventions, it will not be possible to completely blind participants and physiotherapists. To minimise this limitation, it will be explained to participants that the study compares two different approaches for preventing LBP recurrences and participants allocated to usual care group will receive minimal educational intervention. Additionally, researchers responsible for outcome assessments and statistical analysis will remain blinded to group allocation.

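### The named primary analysis and log-rank test carry no health-unit stratum or baseline covariate, and their link to the announced regression models is not stated: valid if run as named, but precision may be given up

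*Protocol article*

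**What the plan says.** All references are to the protocol article.

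- *Randomization and blinding*: permuted blocks of 4 and 6, "in a 1:1 ratio and stratified by HU". *Recruitment* gives 10 health units.
- *Baseline assessment*: every participant completes "a questionnaire of prognostic factors for LBP recurrence and long-term disability". The trial therefore measures, before allocation, variables it regards as predictive of its own primary outcome.
- *Data handling and analysis plan*, Aim I: the opening sentence commits primary and secondary outcomes to multivariable regression, without listing covariates. The primary comparison is then given as follows: "Between-group differences for the primary outcome (risk of LBP recurrence) will be analysed using relative risk reduction", with a 95% interval and a 0.05 significance level. For time to first recurrence: "Secondarily, survival curves for each group will be described and compared (log-rank test". Neither sentence mentions health unit or a baseline factor.
- *Sample size*: the control risk is set by "Assuming a recurrence proportion of 40% in 12 months". With a target of half that risk in the MyBack arm (20%), the section concludes that "a sample size of 81 participants per group will be necessary".

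**The concern.** Stratified allocation balances the arms within each unit. If units differ in recurrence risk, the between-unit part of the variation no longer contributes to the arm difference, but an unstratified variance still counts it. The standard error is then somewhat too large and the test somewhat conservative. Leaving out baseline predictors of recurrence gives up precision in a similar way.

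There is also a question of clarity. A relative risk reduction is an effect measure, not a model, and a log-rank test is not a regression. The opening sentence on multivariable models is not carried into either named analysis. An analyst could report a crude relative risk from the two-by-two table or an adjusted one and comply with the text either way. The two could fall on different sides of 0.05 in a trial with one primary comparison.

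**Working it through.** **1. The plan's own figure.** Inputs from *Sample size*: 0.40 versus 0.20, alpha 0.05 (two-sided assumed, since sidedness is not stated), power 0.80. Pooled-variance formula with mean risk 0.30:

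n = [1.960 × √(2 × 0.30 × 0.70) + 0.842 × √(0.40 × 0.60 + 0.20 × 0.80)]² / 0.20² = (1.270 + 0.532)² / 0.04 = 81.2 per group.

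This reproduces the stated 81, at which power is 79.9%. It is a plain two-proportion calculation with no allowance for strata or covariates.

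**2. Assumed inputs.** The article does not say how much recurrence risk varies between units or how strong the predictors are. Unit effects were taken as normal on the logit scale. Around a 40% risk (logit −0.405), the 95% range of unit risks is −0.405 ± 1.96 × SD, back-transformed:

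| Unit SD (logit) | 95% range of unit risk |
|---|---|
| 0.3 | 27% to 55% |
| 0.5 | 20% to 64% |
| 0.8 | 12% to 76% |
| 1.0 | 9% to 83% |

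A prognostic score with logit SD 0.5 (odds ratio e^0.5 = 1.65 per SD) is called moderate, and SD 1.0 (odds ratio 2.72) strong. Simulated trials had 10 equal units, blocks of 4 and 6, and 158 to 162 evaluable participants. The planned number is 2 × 81 = 162; 93 × 0.85 ≈ 79 per arm gives 158.

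**3. Health unit alone, unadjusted test versus Mantel-Haenszel.** With 160 evaluable:

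| Unit SD | Null rejection, unadjusted / stratified | Power, unadjusted / stratified |
|---|---|---|
| 0 | 4.7% / 4.9% | 79.2% / 79.2% |
| 0.5 | 4.2% / 4.7% | 78.9% / 80.2% |
| 0.8 | 3.8% / 5.4% | 79.6% / 82.8% |

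The gains are 0, 1.3 and 3.2 points. A separate run with 162 evaluable, unit SD 0 to 0.6 and 2,000 trials per setting gave changes of −0.6 to +1.6 points, with unadjusted null rejection of 3.7% to 5.3%. Monte Carlo error on each power figure there is √(0.8 × 0.2 / 2000) ≈ 0.9 points. At SD 1.0, another run put unadjusted null rejection at 3.1% against 4.7% stratified.

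**4. Health unit plus a prognostic score** (162 evaluable; linear model for the risk difference, robust variance with a degrees-of-freedom correction):

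| Unit SD | Score SD | Power, unadjusted → adjusted | Mean SE of risk difference |
|---|---|---|---|
| 0 | 0 | 80.1% → 80.3% | 0.0698 → 0.0706 |
| 0 | 0.5 | 78.7% → 80.3% | 0.0698 → 0.0690 |
| 0.3 | 0.5 | 79.8% → 81.9% | 0.0697 → 0.0684 |
| 0.6 | 0.5 | 79.3% → 82.4% | 0.0696 → 0.0670 |
| 0 | 1.0 | 80.3% → 84.8% | 0.0699 → 0.0654 |
| 0.3 | 1.0 | 81.8% → 86.7% | 0.0698 → 0.0651 |
| 0.6 | 1.0 | 80.8% → 86.8% | 0.0697 → 0.0640 |

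That is about 2 to 3 points for a moderate score and 4 to 6 for a strong one, with the standard error falling 1% to 4% and 6% to 8%. A modified Poisson model with unit SD 0.5 and an odds ratio of 2 per SD gave 80.5% → 85.5%.

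**5. Does unadjusted power fall below plan as units diverge?** With 158 evaluable it was 77.6%, 77.6%, 78.2% and 79.2% at unit SD 0, 0.5, 0.8 and 1.0. It does not fall.

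**6. Log-rank.** Stratifying by unit changed power by about 0 to +2 points.

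**7. The remedy under the null.** With uncorrected robust variance, a modified Poisson model with nine unit terms and one to three covariates rejected 5.8% to 6.3% at unit SD 0 to 0.5 with no predictor effect, and 5.0% to 5.5% otherwise. Mantel-Haenszel stayed at 4.2% to 5.5%.

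**The case against.** The strongest reply is that the analysis section does promise multivariable regression for the primary outcome, and that a relative risk can come straight from such a model. On that reading the later sentence only names the effect measure, and the covariate list belongs in an analysis plan that is not shown. This stands in part. Nothing in the article says that health unit or baseline factors will be left out, so a reader who infers that both are excluded is turning silence into a decision. What remains is that the methods actually named carry no stratum or covariate, that the log-rank test cannot be an instance of the opening sentence, and that the link between model and relative risk is missing.

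A reader might also infer that planned power is lost or that the intervals are certainly too wide. The documents do not support either. The 81 per group is an unadjusted figure, so an unadjusted test delivers what was planned. How much wider the intervals are depends on prognostic strengths that are not given. The larger unit effects imply very wide spreads in risk (12% to 76% at SD 0.8), while *Study design and setting* says that all units recently adopted the same stratified care model. Finally, an adjusted model with many unit terms can itself be slightly anti-conservative, so part of its apparent gain in weak-effect settings may not be real.

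**Conclusion.** The point holds as one of efficiency and clarity, not validity. If the named analyses are run without strata or covariates, type I error stays at or below nominal apart from simulation noise, and planned power is kept. The cost is a possible gain forgone: about 0 to 3 power points for health unit alone (nil if units do not differ, and near 3 only at unit SD 0.8), and about 2 to 6 points when a moderate to strong prognostic factor is also ignored. Most of the benefit comes from the prognostic factors. All these sizes rest on assumed unit and predictor effects, equal recruitment and two-sided testing. The missing link between the regression models and the relative risk rests on the text alone and needs no assumption.

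**What to change.** State in the analysis section that the primary relative risk and its 95% interval are adjusted for health unit and for a short list of baseline prognostic factors, named before unblinding. Two routes are suitable:

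- a standardised logistic or modified Poisson model with a small-sample variance correction; or
- more simply, a Mantel-Haenszel relative risk over health units, which adjusts for unit only.

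Stratify the log-rank test by health unit.

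The cost is a few lines of text and code, with no new data. The downside is sparse strata: 162 / 10 ≈ 16 evaluable participants per unit if recruitment is equal, and about 79 × 0.40 + 79 × 0.20 ≈ 47 events in all. A rule for merging small units must be fixed in advance, the covariate list kept short, and an uncorrected robust variance with many unit terms avoided.
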